### Intervention descriptions

All trial participants will receive care as usual, including information to access a Parents Supervised Driving Program from the Pennsylvania Department of Transportation (PennDoT), as well as information on how to access the PennDoT recommended smartphone app for logging practice hours (RoadReady App). In addition, one group will receive professional BTW with a local driving school instructor (6 h: 4 × 1.5 h lessons), another group will receive ACCEL online hazard skills training (~ 2 h), and another will receive an online active control vehicle and driver safety program (~ 2 h, with no skill training). While the ACCEL intervention is shorter than BTW instruction, this program is designed to be highly interactive and cognitively engaging, focusing specifically on the skill deficits that cause young driver crashes, and thus potentially offsetting the shorter duration. While the online programs can be completed in one sitting, participants can also take breaks and resume where they left off. Adherence (progress and duration) will be tracked via the e-learning platform (ScormCloud) event log and via a quiz and test at the end of the training. For BTW, driving instructors will fill out a brief post-lesson survey to confirm lesson content covered and completion.

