#### In-person behind-the-wheel driver training (BTW)

Professional BTW will be carried out by a third-party accredited driver training school, and their partners. The driving school was chosen for its dual certification for training and license testing and is audited every 6–12 months, giving further support for the integrity of the intervention. The standardized curriculum used for the 6 h of training meets Pennsylvania and national standards, as reviewed by subject matter experts external to the study team from the PA Department of Education, Ohio Traffic Safety Office, and representatives of the American Driver and Traffic Safety Education Association (ADTSEA). Certified PA driving instructors will deliver the training, and school leadership will oversee fidelity through supervision, observations and end-of-lesson surveys completed in REDCap. Staff will also complete brief REDCap surveys (onboarding, post-lesson, offboarding) to monitor student progression and curriculum adherence.

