At the end of the learning/intervention phase, at the point of licensing examination, all participants will complete the following: (i) a second VDA; (ii) PA state licensing examination; (iii) online hazard skills test; (iv) self-report surveys of driving experience (crashes and citations), driving habits and behavior (modified driver behavior questionnaire (mDBQ) [22, 27, 53]; (vi) aggressive driving scale [54, 55]; Youth Risk Behavior Survey [55] Driving items, driving confidence scale [56]); (vii) driving practice quality questionnaire and any other ways they learned to drive beyond the interventions prescribed; and (viii) updated demographic and household factor information (update since T1). Participants who do not pass the state licensing exam initially will be given the opportunity to retake the exam for free and to continue in the trial. All participants who receive a license and remain for post-licensure phase will continue to have their driving trips monitored by the *Way to Drive* and complete surveys at 2, 4, and 6 months, capturing driving behaviors, confidence, crash history, and vehicle access (as at T2 and noted above). We will use multiple imputation and sensitivity analyses to address missing data, and we will report adherence rates for each intervention and for survey completion.

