### Statistical methods

Primary and secondary outcomes will be analyzed by intention-to-treat, with each outcome assessed with a separate model. Results will be interpreted based on both statistical significance (α = 0.05) and effect size, emphasizing clinically meaningful differences. As a secondary analysis, baseline covariates will be included in the model, including age at enrollment, sex, and initial VDA class. Additional factors will be examined as potential confounders (e.g., time between first VDA and licensure) and mediators (e.g., number of practice trips, miles driven, and self-reported practice quality).

To address any non-compliance in the intervention, we will use instrumental variable (IV) analysis [58], which treats the randomization assignment as the instrument. We will also consider principal stratification [59], which can relax some of the assumptions about instrumental variable analysis such as no effect of intervention assignment independent of intervention. Both of these methods attempt to estimate intervention effects among young drivers who would comply with intervention assignment regardless of assigned intervention arm. Compliance will be defined as completing more than 2/3 of the training; in the BTW arm, this would entail completing two of the three lessons. In the ACCEL and active control arms, this would entail completion of at least 2/3 of the content. In follow-up analyses, we will include the proportion of training received as a continuous measure, operationalized as the percentage of lessons completed in the assigned intervention, and utilize the mediation analyses, treating training received as a form of mediation. In all analyses we will consider log or power transformations to reduce skewness in the outcome.

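### The behind-the-wheel compliance cut-off fits neither the four-lesson schedule nor its own two-thirds rule, and the own-arm training percentage is a poor mediator as written

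*Protocol article*

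**What the plan says.** Three places in the protocol article bear on this point.

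- **Schedule.** Under Intervention descriptions, one arm receives "professional BTW with a local driving school instructor (6 h: 4 × 1.5 h lessons". The section on in-person behind-the-wheel (BTW) training gives the same total: "The standardized curriculum used for the 6 h of training meets Pennsylvania and national standards".
- **Compliance rule.** Under Statistical methods: "Compliance will be defined as completing more than 2/3 of the training". This is then translated arm by arm. For BTW, "in the BTW arm, this would entail completing two of the three lessons". For the online programmes, "In the ACCEL and active control arms, this would entail completion of at least 2/3 of the content". The rule serves an instrumental-variable (IV) analysis with randomization as the instrument and, as an option, principal stratification. Both aim at drivers who would follow whichever arm they were allotted.
- **Continuous measure.** The same section adds follow-up analyses, including mediation, that use the proportion of training received, "operationalized as the percentage of lessons completed in the assigned intervention".

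Separately, the post-intervention (T2) survey listed under Other measures asks about "any other ways they learned to drive beyond the interventions prescribed". Primary and secondary outcomes are analysed by intention-to-treat.

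**The concern.** The compliance rule is stated three ways that do not agree, and the BTW version counts lessons on a schedule that appears nowhere else in the article. Whoever codes the analysis must choose between the sentences. If that choice is made after outcomes are known, the complier population is no longer fixed in advance.

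The continuous measure has a different weakness. It records how much of the assigned programme each person finished. The control programme is described as having no driving skills content, yet a control participant who finishes it scores 100%, the same as a participant who finishes BTW or ACCEL. A mediator that takes the same value with and without skills training cannot carry the effect of skills training.

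**Working it through.** **Inputs.** Four lessons of 1.5 h (Intervention descriptions); 6 h in total (the same section and the BTW section); a general rule of strictly more than 2/3, a BTW rule of two lessons out of three, and an online rule of at least 2/3 (all Statistical methods).

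**Step 1: is the schedule consistent with itself?** 4 × 1.5 h = 6 h, which agrees with both statements of the total. Three such lessons would be 3 × 1.5 h = 4.5 h, which does not.

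**Step 2: does the BTW cut-off follow from the general rule?** Compare k/L with 2/3 = 66.7%:

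| Lessons completed / planned | Share | More than 2/3? | At least 2/3? |
|---|---|---|---|
| 2 / 3 | 66.7% | no | yes |
| 3 / 3 | 100% | yes | yes |
| 2 / 4 | 50% | no | no |
| 3 / 4 | 75% | yes | yes |

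The plan's cut-off of two lessons cannot be reproduced from its own general rule on either schedule. With three lessons it meets only the online arms' inequality. With four it meets neither.

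**Step 3: what does the discrepancy do to the IV estimate?** In its simplest (Wald) form, the complier effect is the intention-to-treat effect divided by the difference between arms in the share treated. Let c be the share of the BTW arm completing three or more of four lessons, and x the share stopping at exactly two. With no outside training counted, the denominator is c + x if two lessons suffice and c if they do not. The two complier effects differ by the factor (c + x)/c. The article gives neither share, so both are assumed:

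| c | x = 0 | x = 0.05 | x = 0.10 |
|---|---|---|---|
| 0.70 | 1.00 | 1.07 | 1.14 |
| 0.80 | 1.00 | 1.06 | 1.12 |
| 0.90 | 1.00 | 1.06 | 1.11 |

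**Step 4: what does the own-arm percentage do as a mediator?** Suppose mean completion is the same in the BTW and control arms, at 70% to 90% (assumed). On the own-arm scale, the difference between arms is 0.90 − 0.90 = 0 at the upper end and 0.70 − 0.70 = 0 at the lower. An indirect effect formed as (arm to mediator) × (mediator to outcome) is then 0, even if training works. Scored as share of BTW completed, with 0 for those who had none, the difference is 0.70 to 0.90.

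**The case against.** The strongest reply is that nothing here touches the main result. The primary analysis is by intention-to-treat, the sample size does not depend on compliance, principal stratification is only to be considered, and the lesson-count error reclassifies only those who stop at exactly two lessons. All of that stands, and it limits the severity. The inequality mismatch is also minor: on four lessons both wordings require three, and in the online arms they differ only for someone at exactly two thirds.

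A reader might go further and infer that the IV and principal-stratification analyses rest on a wrong treatment variable because compliance is judged within the assigned arm. The document does not support that. The stated target is people who would comply under any allocation, and that group can be defined only if compliance has a meaning in every arm, control included. The phrase about the assigned intervention belongs only to the follow-up continuous and mediation analyses. The mediator model itself is not given, so Step 4 describes the measure as worded.

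A reader might also infer that lessons bought privately by ACCEL or control families bias the complier effect by a known amount. With 80% completion and 10% to 30% crossover, the factor would be 0.80/0.70 = 1.14 to 0.80/0.50 = 1.60. Every one of those rates is assumed, and the article reports none. It does not say that outside training is excluded from the model, and an article may leave that detail to the analysis plan. Treating outside learning as part of usual care is also a legitimate choice of estimand.

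**Conclusion.** The contradiction is certain and needs no outside fact: four lessons in one section, three in another, and a two-lesson cut-off that fails the general rule on both. Its effect is confined to the IV and principal-stratification analyses. The factor of 1.00 to about 1.14 rests on assumed completion of 70% to 90% and an assumed 0 to 10% stopping at two lessons.

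The own-arm percentage is a poor mediator as worded. The near-zero indirect effect holds if completion is similar across arms and if finishing the control course is scored as training.

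The size of any bias from outside training cannot be computed from the document. This should be fixed, but it does not threaten the primary conclusion.

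**What to change.** 1. Reconcile Intervention descriptions and Statistical methods on the number of BTW lessons. This review takes no position on which schedule is right.
2. State one compliance threshold, with one inequality, as a share of the planned programme, and apply it to all three arms. Give the resulting whole-lesson count for BTW so that it can be checked against the rule.
3. For the follow-up continuous and mediation analyses, replace the own-arm percentage with two exposures: share of BTW completed and share of ACCEL completed. Each is 0 for participants who received none, so that completing the control course does not count as training.
4. As a sensitivity analysis, count outside professional training reported at T2, as far as that item records it.

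The cost is wording and minor coding. Instructor reports and e-learning logs already supply the adherence data. The T2 item is not shown to record professional lessons or hours, so item 4 may need one clarified question. Data collection is ongoing and no interim analyses are planned, so the rule can be settled before outcomes are analysed.

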### Objectives

The primary objective of the DRIVER (DRIVer Education Research) study is to quantify the extent to which modern online driver training and BTW prior to licensure can add protection beyond GDL against crash risk early in licensure. The secondary objective is to quantify the effect of driver training on skill acquisition. The study aims and outcomes are summarized in Table 1. We hypothesize that both ACCEL and BTW training will reduce crash risk and improve driving skills compared to the control group. More specifically, we hypothesize that ACCEL will show greater improvement in crash risk and skills than BTW on the theory that ACCEL is more targeted to the critical reasons for crashes among novice adolescent drivers. However, we expect BTW to perform better on PA license examination outcomes since this test measures skills directly trained by BTW. We also hypothesize that those with weakness in cognitive and attentional control will benefit most from the training interventions in the key outcomes, and those with personality differences and risky driving practices linked to crash risk may be more resistant to the effects of driver training.

**Table 1 Tab1:** Summary of study aims and associated outcomes

Study Aim	Primary Outcome	Secondary Outcome
**Aim 1**. Determine the effect of driver training (ACCEL or BTW) compared to GDL alone on post-licensure crash risk	Hard Braking Events per 100 miles driven via Way to Drive monitoring app	• Phone Use while Driving (minutes per hour of driving) • Speeding (proportion of time > 10 miles over posted speed limit) • Self-reported crash involvement • Self-reported risky driving behavior
**Aim 2**. Determine the effect of driver training (ACCEL or BTW) compared to GDL alone on skill acquisition	Pass rate on the first attempt at the state licensing examination	• Virtual Driving Assessment (VDA) Performance at T2 • Change in T1-T2 VDA performance • Number of license exam attempts
**Aim 3**. Identify age-related risk factors for crashes that may moderate the response to training	Interactions with Aim 1 & 2 outcomes	Interactions with Aim 1 & 2 outcomes

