#### Primary outcomes

There are two primary outcomes. First, crash risk in the first 2 months of licensure (Aim 1 and 3) will be measured as the rate of hard braking events per 100 miles driving, captured via the Way to Drive smartphone app. Monitoring of hard braking events will continue through 6 months to assess crash risk at 6 months also. The app, provided by Cambridge Mobile Telematics, deploys the same algorithms as leading usage-based automobile insurance programs to measure risky driving behaviors (phone use during trips, speeding, and other kinematic risky driving measures) [38]. Second, driver skills at licensure (Aim 2 and 3) will be measured as the pass rate on the first attempt of the state licensure examination. While the state licensing exam assesses a limited set of procedural driving skills, it provides a standardized, real-world benchmark of basic driving competence and is a relevant proximal outcome for novice drivers.

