Attrition is expected to be modest given the trial's retention strategies, for an estimated final sample size between 800 and 1000 participants. Participants lost before or during the intervention phase may be replaced. Participants who drop out after intervention but before the licensure exam will be encouraged to complete a second VDA. Data for available outcomes to this point will be considered for these participants, and outcomes that can be feasibly imputed will be included in analysis. For participants who fail their initial licensure exam, the study will fund a second attempt and if they pass, they will continue in the trial and follow-up data will be collected. For the rare individuals who fail the second attempt, if they go on to pass on a subsequent attempt (not provided by the study) within the study window, their follow-up data will be collected post-licensure. If the participant does not pass their licensure exam within the study window, they will not be replaced; instead, data for available outcomes will be considered for analyses, with other outcomes imputed as feasible using the data sources noted above.

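### Post-licensure driving outcomes may be imputed for participants with no license in the study window, for whom those outcomes are undefined

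*Protocol article*

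**What the plan says.** The last paragraph of Statistical methods deals with participants who remain unlicensed: "If the participant does not pass their licensure exam within the study window, they will not be replaced". It then gives the rule for their data: "instead, data for available outcomes will be considered for analyses, with other outcomes imputed as feasible using the data sources noted above". The same section puts all primary and secondary outcomes under intention-to-treat.

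Primary outcomes defines the Aim 1 endpoint so that it starts at licensure: "crash risk in the first 2 months of licensure (Aim 1 and 3) will be measured as the rate of hard braking events". Secondary outcomes adds phone use, speeding, self-reported crashes and self-reported risky driving, all after licensure. Other measures confirms who supplies these data: "All participants who receive a license and remain for post-licensure phase will continue to have their driving trips monitored".

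The second primary outcome, in Table 1 under Objectives, is "Pass rate on the first attempt at the state licensing examination". On that exam the authors write: "we expect BTW to perform better on PA license examination outcomes since this test measures skills directly trained by BTW". Sample size says the trial can detect between-group differences of 15 to 19% in pass rates.

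Principal stratification appears in Statistical methods, but only for compliance with the assigned training.

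**The concern.** By the end of the window, someone who tried and failed has a known exam result and a known number of attempts, and a second VDA if it was done. What remains is mainly the post-licensure set, including the primary hard-braking rate. A person with no license in the window has no licensed miles, no qualifying events and no date from which to count 2 months. The rate is therefore undefined, not unrecorded. No unlicensed participant has an observed value, so any imputation model must borrow from licensed drivers and cannot be checked against data.

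Licensure also happens after randomization and depends on passing an exam that one arm is expected to pass more often. If the arms differ in who gets licensed, the groups with real driving data differ in composition. The text does not say which treatment effect the imputed analysis would estimate. The wording as feasible also leaves the choice of what to impute on a primary outcome open until data are in hand.

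**Working it through.** The point disputes no figure in the plan. The nearest one reproduces: 333 × (1 − 0.20) = 266.4, stated as 266 per arm. The check below asks how far the arms could differ in licensure, and what that would do to a comparison of licensed participants.

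**Inputs from the article.** A pass-rate difference of 15 to 19%, read here as percentage points; a funded second attempt, with later attempts allowed within the window; second failures described as rare, without a figure; a target 20% reduction in hard braking, so a rate ratio of 0.80.

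**Assumptions (the article gives no values).** Control first-attempt pass rate p of 60 to 80%; the same pass chance at each retest; extra licensees in the trained arm brake hard at r = 1.25 to 2 times the rate of the others; training has no effect on braking.

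**Step 1: share unlicensed after k attempts.** Control: (1 − p)^k. Trained arm with gain d: (1 − p − d)^k.

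| p | d | Control, k=2 | Trained, k=2 | Gap, k=2 | Gap, k=3 |
|---|---|---|---|---|---|
| 0.60 | 0.15 | 0.160 | 0.062 | 0.098 | 0.048 |
| 0.60 | 0.19 | 0.160 | 0.044 | 0.116 | 0.055 |
| 0.70 | 0.15 | 0.090 | 0.023 | 0.068 | 0.024 |
| 0.70 | 0.19 | 0.090 | 0.012 | 0.078 | 0.026 |
| 0.80 | 0.15 | 0.040 | 0.002 | 0.037 | 0.008 |
| 0.80 | 0.19 | 0.040 | 0.000 | 0.040 | 0.008 |

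The gap is about 4 to 12 points after the two funded attempts and about 1 to 5.5 points after three. After two attempts, about 13 to 53 of 333 control participants and 0 to 21 of 333 trained participants would be unlicensed.

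**Step 2: licensed-only rate ratio with no training effect.** Let u_C and u_T be the unlicensed shares in the control and trained arms. Participants licensed under either arm have relative rate 1. A share u_C − u_T is licensed only if trained and has rate r. Then

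ratio = [(1 − u_C) + (u_C − u_T) × r] / (1 − u_T).

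- Low end, shares of 5% and 1%, r = 1.25: (0.95 + 0.04 × 1.25) / 0.99 = 1.010.
- Middle, shares of 9% and 2.3%, r = 1.5: (0.91 + 0.067 × 1.5) / 0.977 = 1.034.
- High end, shares of 16% and 4.4%, r = 2: (0.84 + 0.116 × 2) / 0.956 = 1.121.

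The range is about 1.01 to 1.12, where the true ratio is 1.00. These shares are close to the two-attempt rows of the table. With three attempts the ratio is nearer 1: at the largest three-attempt gap (6.4% against 0.9%) and r = 2 it is (0.936 + 0.055 × 2) / 0.991 = 1.056.

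**What the numbers measure.** They give the selection bias of comparing licensed participants only. They do not measure the bias of imputation, which depends on an imputation model that the article does not describe.

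**The case against.** The strongest defense has several parts.

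- **The wording is loose.** The text says as feasible and names no post-licensure outcome. The clause also covers people who never attempt the exam, whose exam and second-VDA results can sensibly be imputed. It refers to the study window, and for someone licensed later the first 2 months exist but are unobserved. All of this stands and limits the point to post-licensure outcomes in participants known to be unlicensed at the end of the window.
- **First-attempt pass is not licensure.** Retakes exist so that early failures can still be licensed, eligibility requires a plan to get a license, and second failures are called rare. This stands: an effect on licensure is inferred from a hypothesis about the exam, and the gap may be small.
- **Imputing a rate as if the person had been licensed is a legitimate hypothetical estimand, and the details belong in the SAP.** Such an estimand could be defended, and a model using VDA and exam data might reduce selection. The article states no such estimand, however. It states a rule for these participants, so this is not simply a detail left to another document.

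A reader might infer more than the article supports:

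- *The standard error would treat non-drivers as observed data.* Properly combined multiple imputation carries between-imputation variance, so this does not follow.
- *Selection by arm would be hidden.* First-attempt pass and number of attempts are trial outcomes, and CONSORT reporting is promised.
- *Most of the first-attempt difference carries through to licensure.* Take 75% against 90% licensed with r of 1.5 to 2. The shift would be (0.15 / 0.90) × 0.5 to 1.0, or 8.3 to 16.7%. But 75% licensed after two attempts at a constant pass chance needs half to fail each time (0.5² = 0.25), which sits badly with second failures being rare.

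**Conclusion.** The point holds in this limited form. The article's rule permits imputation of the Aim 1 primary outcome, and of the other post-licensure outcomes, for people in whom they are undefined. Nothing else in the text handles selection into licensure, because principal stratification is reserved for compliance.

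The size is unknown and may be small. The illustrative ratio of 1.01 to 1.12 rests on assumed pass rates, constant retest chances and an assumed braking multiplier. It describes the bias of a licensed-only comparison, so it is also a caution against simply replacing imputation with an unqualified licensed-only analysis. The case for changing the rule is that it imputes a quantity that does not exist for these participants and fixes no estimand. It does not depend on any demonstrated large bias. The point does not extend to participants who drop out before the exam and may be licensed later; the article treats them separately and imputation can be meaningful for them.

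**What to change.** 1. State the Aim 1 estimand, including how participants who are unlicensed at the end of the window enter it.
2. Do not impute post-licensure driving outcomes for participants known to be unlicensed at the end of the window. Limit imputation of these outcomes to licensed participants with missing app data and to participants whose license status is unknown.
3. Label the comparison of licensed participants as conditional on licensure, and report the licensed proportion by arm beside it.
4. Add a principal-stratum analysis of those who would be licensed under either arm, with bounds, to address selection. The method is already cited for compliance.
5. Keep imputation for exam and VDA outcomes where sensible, with a sensitivity analysis that counts never-attempted as not passed.

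The cost is revised wording, one extra analysis for selection, the exam sensitivity analysis, a smaller nominal n for Aim 1, and a crash-risk claim that is explicitly about licensed drivers. Data collection is ongoing and no interim analyses are planned, so the change can still be made before outcome data by arm are seen.
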